### Feasibility

At University Hospital Heidelberg (Department of General, Visceral, and Transplant Surgery) 146 pancreatectomies are done every year, of which 48 and 98 are total and subtotal/distal pancreatectomies, respectively. These values were determined in 2009; values in 2010 have yet to be determined. DISPACT (ISRCTN18452029) [13,14], a trial examining techniques for closure of the remnant pancreas in distal pancreatectomy applied similar eligibility criteria, and confirmed that six patients could be enrolled every month. Therefore, the target sample size is achievable. Accounting for a slow starting period, recruitment is expected to take about 8 months.

### Interim analyses and stopping guidelines

Once 20 patients have been included, an interim analysis will be carried out with the possibility to stop the study for futility. This interim analysis is based on the conditional power approach [15]. Under the assumption of sufficient power (i.e., the probability that the alternative hypothesis is true, by a sufficient margin from the null hypothesis), the margin for the distribution of the test statistic $Z=\frac{\left|\bar{d}\right|+\;2s_{d}-\lambda }{\sqrt{3/ns_{d}^{2}}}$ is $\theta =u_{1-\alpha }+u_{1-\beta }$, where *u*_*l*_ is the *l*-quantile of the standard normal distribution. The interim test statistic is calculated as $Z_{1}=\frac{\left|\bar{d}\right|+\;2s_{d_{1}}-\lambda }{\sqrt{3/n_{1}s_{d}^{2}}}$, where *λ* = 20% is the 20% limit, and *Z*_1_, *d*_1_, and *n*_1_are the respective values after enrolling the first 20 patients. Given $\theta =u_{1-\alpha }+u_{1-\beta }$, the conditional power to successfully reject the null hypothesis is below 30% if *Z*_1_ > 0.813 for *n*_1_ = 20. If the alternative hypothesis is true and the true power is 80%, the probability of obtaining this result is < 0.05%, resulting in a nominal power of 79.95%. The interim analysis will safeguard against the situation where the level of agreement is too low for the study to justifiably continue.

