### Sample size

The agreement between the two devices will be quantified using the approach suggested by Bland and Altman, in which the 95% limits of agreement with 95% CIs will be compared with a prespecified, clinically acceptable relative difference [9] of 20%. The standard error of the 95% limits of agreement is approximately $\mathrm{se}\approx \sqrt{\frac{3s_{d}^{2}}{n}}$, where $s_{d}$ is the standard deviation of the differences between the two devices and n is the sample size (number of paired values the differences are calculated from). The sample size is dependent on the intended width of the CIs. Bland and Altman recommend a sample size of 100, which gives a 95% CI of about ± 0.34$s_{d}$, or about one-sixth of the width of the actual agreement. The power to reject the hypothesis that the prespecified limits of agreement of ± 20% are violated is > 80% if $\frac{\delta +\;2\sigma -\;\lambda }{\sqrt{\frac{3\sigma^{2}}{n}}}<-\;2.486$, where λ is the 20% limit and *δ* and $\sigma^{2}$ represent the expected value and variance of *d*, respectively. This inequality may be approximated by δ+2.5σ<λ indicating that the power is sufficient with *δ* = 5% and *σ* = 6%, for example. To fulfil the sample size recommended by Bland and Altman (i.e., ≥ 100 pairs of values), we plan to enrol up to 130 patients in this study.

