### Statistical methods

The test statistic for testing the null hypothesis $H_{o}:\left|\delta \right|+2\sigma >\lambda$ is calculated as $Z=\frac{\left|\bar{d}\right|\pm 2s_{d}-\lambda }{\sqrt{3/ns_{d}^{2}}}$, where λ=20% for the outcome measure. Its distribution under $\left|\delta \right|+2\sigma =\lambda$ is asymptotically normal. Therefore, the null hypothesis is rejected if *Z* is below the 0.05 quantile of the normal distribution. Descriptive statistics of continuous variables and scores include the number of observations, the mean and standard deviation, the median, minimum, and maximum. Descriptive statistics of categorical variables (nominal or ordinal) include absolute and relative frequencies (n and per cent). The primary outcome measure is the level of agreement in blood glucose levels determined by the CGM and a BGA, assessed 8 h after the initial placement and calibration of the CGM using the relative difference $\bar{d}$, as described above. Bland and Altman plots will be drawn, including the CIs for the mean difference and limits of agreement to show the agreement between the pairs of values [9,21]. Secondary analyses, including the level of agreement between the two devices at each time after placement and calibration of the CGM will be analysed descriptively, while applying the same equivalence bounds used in the primary analysis. A linear mixed model will be developed using time as the fixed factor. Subject and the interaction subject × time will be included as random explanatory variables. The individual values $\bar{d}$ at all times up to 8 h will be included as the response variable. This model will be used to impute missing data. Biometric analysis will be defined in the statistical analysis plan, which must be authorised before the database is opened by the biostatistician, the sponsor, and the principal investigator.

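### The futility limit Z1 > 0.813 is on a different scale from the Z1 it is applied to, so the stated 30% conditional power and <0.05% stopping probability do not hold; the practical cost is small

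*Protocol article*

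**What the plan says.** The section Interim analyses and stopping guidelines of the protocol article sets one look: "Once 20 patients have been included, an interim analysis will be carried out with the possibility to stop the study for futility". The rule uses conditional power under the design alternative, with drift θ = u(1−α) + u(1−β) for the final statistic. The interim statistic Z1 is the observed upper limit of agreement minus 20%, divided by a standard error computed with n1 = 20.

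Three properties are then given:

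- "the conditional power to successfully reject the null hypothesis is below 30% if" Z1 > 0.813 at n1 = 20.
- "If the alternative hypothesis is true and the true power is 80" per cent, this result has a probability below 0.05%.
- The rule leaves the design almost untouched, "resulting in a nominal power of 79.95" per cent.

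The other inputs are in neighbouring sections. Statistical methods makes the test one-sided at 5%: "Therefore, the null hypothesis is rejected if *Z* is below the 0.05 quantile of the normal distribution". Sample size gives the constant 2.486 and two candidate final sizes: "Bland and Altman recommend a sample size of 100" and "we plan to enrol up to 130 patients in this study". The interim section does not say which final n was used.

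**The concern.** A statistic divided by its own standard error has unit variance. The usual conditional-power algebra first yields a limit for √(n1/n)·Z1, which must then be divided by √(n1/n) to become a limit for Z1. The printed limit looks as if that last step was left out. The printed stopping probability also looks too small for a look at one fifth of the data.

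This is the study's only stopping rule. If limit, conditional power and stopping probability cannot all be true together, the rule as written stops studies that its own 30% criterion would let continue. Whoever has to decide on stopping would also be relying on a wrong error rate.

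**Working it through.** **Inputs.** One-sided α = 0.05, so reject if Z < −1.645 (Statistical methods). Power 80% (interim section), so θ = 1.645 + 0.842 = 2.486 (rounded; also in Sample size). n1 = 20 (interim section). n = 100 pairs (Sample size), so t = 20/100 = 0.20 and √t = 0.447. I read the interim standard error as √(3s²/n1), in line with Sample size. The 20% margin cancels.

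**Formula.** The final Z equals √t·Z1 plus an independent increment with mean −θ(1−t) and variance 1−t. Hence

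CP(Z1) = Φ{[−1.645 − √t·Z1 + θ(1−t)] / √(1−t)}.

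**Reproducing 0.813.** Setting CP = 0.30, where Φ⁻¹(0.30) = −0.524:

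√t·Z1 = −1.645 + 2.486 × 0.8 + 0.524 × √0.8 = 0.813.

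This is the printed number to three decimals, but it is the limit for √t·Z1. For Z1 itself the limit is 0.8134/0.447 = 1.819. With n = 130 the same steps give 0.941 and 2.40, so the printed value points to n = 100.

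**Conditional power at the printed limit.** CP(0.813) = Φ{[−1.645 − 0.364 + 1.989]/0.894} = 49.1%. With n = 130 it is 56%. Other readings do not give 30% either: one-sided 2.5% gives 46%, drift at the null boundary 1.2%, and the observed trend less than 0.01%.

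**Stopping probability.** Under the alternative, Z1 has mean −2.486 × 0.447 = −1.112.

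- Printed limit: 1 − Φ(0.813 + 1.112) = 2.7%.
- Rescaled limit: 1 − Φ(1.819 + 1.112) = 0.17%.
- Printed figure: 1 − Φ(0.813 + 2.486) = 0.048%, which uses the full-trial drift at 20 patients.

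The stated power is 80% − 0.05% = 79.95%, so it carries the same error.

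**Power with stopping** (bivariate normal, correlation 0.447): 78.9% at 0.813 and 79.96% at 1.819.

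**Simulation of the actual statistic.** Normal differences, δ = 5%, σ = 15/(2 + 2.486√0.03) = 6.17%, n1 = 20, n = 100, 200,000 to 400,000 runs per simulation, power without stopping about 79%.

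| Z1 limit | Quantity | Stated | Large-sample | Simulated |
|---|---|---|---|---|
| 0.813 | Conditional power at limit | below 30% | 49.1% | about 36% |
| 0.813 | Stopping probability | <0.05% | 2.7% | 1.6% |
| 0.813 | Power lost (points) | 0.05 | 1.1 | 0.4 to 0.5 |
| 1.82 | Conditional power at limit | – | 30% | about 9% |
| 1.82 | Stopping probability | – | 0.17% | about 0.015% |

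The 9% is imprecise: only about 126 runs fall near Z1 = 1.82, and a repeat with another seed gave about 5%. Either value is far below 30%.

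**The case against.** The strongest reply is that the large-sample figures exaggerate the fault. Z1 divides by a standard deviation estimated from 20 patients, so it is skewed and not well described by a normal law. This stands. Simulated conditional power at 0.813 is about 36%, and averaged over the whole region Z1 > 0.813 it is about 28%. A reader might infer from the 49% that the rule abandons studies with an even chance of success. That is not supported for the statistic the trial would compute near its 80%-power design. The stated property, however, is that conditional power is below 30% wherever Z1 exceeds 0.813. That fails at the limit in both calculations. A stopping probability of 1.6% is also more than 30 times the stated ceiling.

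A reader might also infer that replacing 0.813 by 1.82 repairs the rule. It does not: in simulation 1.82 misses the 30% target by more than 0.813 does. In the normal approximation it also cuts stopping at the null boundary from 21% to 3.4%, which weakens the safeguard the look is meant to provide. The value depends on n = 100 as well.

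Finally, the look only permits stopping and cannot raise the type I error. Stopping requires an observed limit of agreement already beyond 20%. The stated 79.95% nearly equals the 79.96% obtained on the rescaled limit. All of this stands and limits the severity. The agreement in power is a coincidence, since the printed figure comes from subtracting a wrongly computed stopping probability.

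**Conclusion.** The rule is wrong as written. The limit belongs to √(n1/n)·Z1 but is applied to Z1, and the stopping probability uses the full-trial drift of 2.486 instead of 1.11. In the protocol's own normal approximation with n = 100, the <0.05% is not met on either scale (2.7% or 0.17%). For Z1 > 0.813 the stated 30%, <0.05% and 79.95% become about 49%, 2.7% and 78.9%. Simulation gives about 36%, 1.6% and 0.4 to 0.5 points of power lost.

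The first set rests on asymptotic normality and on n = 100, which is inferred because it alone, of the sizes tried from 100 to 130, reproduces 0.813. The second rests on normal differences with δ = 5% and σ = 6.17%; δ = 2% with σ = 7.4% gave much the same (39%, 1.6%, 0.46 points).

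This is a correction of stated figures. A stronger reading, that the primary conclusion is at risk, has no support: the final test and its type I error are not harmed by a look that can only stop for futility.

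**What to change.** Before the 20-patient look, by amendment or in the statistical analysis plan, take one of two routes.

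1. **Keep the 30% criterion.** State the final n. Put limit and statistic on the same scale; the large-sample limits for Z1 are 1.82 for n = 100 and 2.40 for n = 130. Then set the limit actually used, its stopping probability and the resulting power by simulating the statistic itself, because the large-sample 1.82 does not deliver 30%.
2. **Keep Z1 > 0.813.** Replace 30%, <0.05% and 79.95% by its real properties: about 49%, 2.7% and 78.9% in large samples, or about 36%, 1.6% and 0.4 to 0.5 points of power lost by simulation.

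Either way, name the method behind each figure. The cost is a short simulation and a few changed sentences, with no extra patients.

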### Sampling method

The CGM assesses blood glucose levels from a microdialysate of the circulating blood by an amperometric technique. In brief, acetated Ringer’s solution (perfusate) is delivered through a microdialysis probe. Solute exchange occurs in both directions across the semipermeable membrane of the microdialysis probe and enriches the perfusate by a fraction of the blood glucose level. This fraction is referred to as the relative recovery. Knowledge of the relative recovery rate is essential to determine solute levels [16]. The CGM is calibrated before implantation and is immediately referenced. Patency of access to the vascular bed is maintained by programmed infusion of normal saline solution supplemented with 1,000 IU/L heparin (flushing medium).

At the University Hospital Heidelberg (Interdisciplinary Operative Intensive Care Unit) point-of-care blood gas analyses are done using a RAPIDLab® 1265 blood gas analyser (BGA; Siemens Healthcare Diagnostics GmbH, Bad Nauheim, Germany). The BGA assesses blood glucose levels from lithium heparinised whole blood, also by an amperometric technique.

In brief, the amperometric technique involves the conversion of glucose and oxygen in water to gluconolactone and hydrogen peroxide, in a reaction catalysed by glucose oxidase. The concentration of glucose in the sample is determined indirectly as the amount of hydrogen peroxide yielded by the reaction. Hydrogen peroxide is detected on the surface of a platinum electrode upon oxidation resulting in a change of the electrochemical potential [17].

At the University Hospital Heidelberg (Central Laboratory), an ADVIA® 2400 Chemistry System (Siemens Healthcare Diagnostics GmbH) is used to measure blood glucose levels in routine clinical practice. This system measures blood glucose levels in fluoridated plasma by the hexokinase/glucose 6-phosphate dehydrogenase method. Glucose is phosphorylated to glucose 6-phosphate in the presence of ATP by hexokinase. Then, glucose 6-phosphate is dehydrogenated in the presence of NADP to 6-phosphogluconate by glucose 6-phosphate dehydrogenase. This reaction also yields NADPH2, which is measured by the system.

The hexokinase/glucose 6-phosphate dehydrogenase method is considered the reference method for assessing blood glucose levels, including in routine clinical practice. So far, no drugs are known to interfere with this measurement system [18].

All blood samples are to be collected from the site of insertion of the central venous catheter, as all blood samples will be collected from one lumen of the central venous catheter. Lithium or fluoride will be added to the blood samples and all blood samples will be processed immediately. The blood samples collected in lithium-heparinised tubes (Blutgas-Monovette®; Sarstedt AG & Co., Nümbrecht, Germany) used to assess agreement between the CGM and a BGA will be processed within 5 min. The blood samples collected in fluoride tubes (S-Monovette® Glukose; Sarstedt AG & Co.) used to independently confirm the results determined by a point-of-care BGA will be kept on ice until being sent to the central laboratory.

### Measurement process

All subjects will first enter a screening stage lasting up to 1 month, and an additional 2-h reference period before the study period. The study will consist of a 24-h measurement period and a 48-h follow-up period. During the measurement period, blood samples will be obtained 13 times. The overall duration of the measurement stage will be determined by the duration of intensive care.

### Screening (Visit 1)

All patients admitted to University Hospital Heidelberg will be assessed for eligibility after being fully informed of all aspects of the study that are relevant to their decision to participate. Patients will be asked to sign and date an informed consent form [19]. After providing consent, the subjects will undergo screening, which will involve assessment of baseline characteristics and medical history (Table 2).

**Table 2 T2:** Study timetable

	**Visit 1**	**Visit 2**	**Visit 3 - 9**	**Visit 10**	**Visit 11 -12**	**Visit 13**	**Visit 14**	**Visit 15**
	up to one month and a reference period^1^ of 2 h before Visit 2	0 h^2^	1–7 h (every hour) ± 5 min	8 h ± 5 min	9 and 10 h ± 5 min	16 h ± 30 min	24 h ± 30 min	72 h ± 1 h
Informed consent	●							
Eligibility criteria	●	●						
Medical history	●							
Concomitant medication	●	●	●	●	●	●	●	●
Physical examination	●						●	
Vital signs^3^	●	●	●	●	●	●	●	●
Pregnancy test^4^	●							
Placement of the CGM		●						
CGM calibration		●						
Continuous glucose and lactate monitoring		●	●	●	●	●	●	up to every 2 h
Recalibration				●				
Central venous blood sampling for the BGA^5^			●	●	●	●	●	
Central venous blood sampling for central laboratory measurement^6^		●		●		●	●	
Removal of CGM								●
Assessment of unwanted events/effects		●	●	●	●	●	●	●

^1^ Priming, tempering and transient oscillation of the sensor systems.

^2^ Within 2 h of transfer to the recovery room or intensive care unit.

^3^ Heart rate, blood pressure, and tympanic body temperature.

^4^ Only females with reproductive potential.

^5^ Samples used to assess blood glucose, blood lactate, haematocrit, and haemoglobin.

^6^ Samples used to assess blood glucose and blood lactate levels.

CGM: continuous glucose monitor; BGA: blood gas analyser.

### Study period (Visits 2–14)

All subjects will be treated according to the local standards at the University Hospital Heidelberg. After successful induction of anaesthesia, a multi-lumen central venous catheter will be implanted in all patients. Perioperative antibiotic prophylaxis (e.g., 4 g mezlocillin and 500 mg metronidazole) will be administered approximately 30 min before commencing surgery, and will be repeated if the duration of surgery exceeds 4 h. Perioperative prophylaxis with unfractionated or fractionated/low-molecular-weight heparin will be administered to prevent venous thromboembolism. Patients will be closely monitored throughout surgery and the post-operative period.

Within 2 h after transfer to the recovery room or an intensive care unit, the patients will be re-assessed for eligibility and the planned measurements will be commenced, as summarised in the Figure 1 and Table 2. Unless medical reasons preclude entry into the study (i.e., a lumen is not required for medical purposes, such as perioperative fluid therapy and medications) the patients will be fitted with the CGM according to the manufacturer’s instructions. The device is to be primed, connected to the patient, and referenced to the blood glucose level measured by a BGA. This point represents the start of the measurement period (1 h before the first measurement).

**Figure 1 F1:**
[figure not shown]
**Timeline.** PC: Priming and Calibration Period (Priming, tempering, transient oscillation and initial calibration of the sensor from the Continuous GlucoseMonitor); R: Referencing; Rec: Recalibration (duration = 10 min including washing); M: Glucose and Lactatemonitoring; B: Blood sampling for comparison (glucose, lactate, haemoglobin, haematocrit); L: Blood sampling for central lab (glucose and lactate).

For the next 10 h, the patients will be visited by the research staff every hour. At each visit, the CGM value will be recorded and blood samples will be collected for measurement by a BGA. At 0 and 8 h (Visits 2 and 10, respectively), additional blood samples will be collected and measured using the ADVIA 2400 Chemistry System to independently confirm the blood glucose measurement. Using the value obtained at 8 h (Visit 10), the CGM will be re-calibrated and further values will be recorded at 9, 10, 16, and 24 h. At 16 and 24 h (Visits 13 and 14, respectively), additional blood samples will be collected. Visit 14 represents the end of the measurement period. The CGM is left in place until Visit 15.

No subjects will be fitted with the CGM unless central venous cannulisation was necessary for medical reasons. The central venous catheters will be removed when clinically indicated. No subjects will be equipped or re-equipped with central venous catheters unless there is a clear medical reason. If discharge from the recovery room or intensive care unit occurs within 24 h, Visit 14 will be brought forward and the CGM will be removed.

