### Objectives

The objective of the CONTinuous ASSessment of blood GLUcose (CONTASSGLU) study is to evaluate the clinical use of the CGM performed via a central vein, and to determine the impact of phenomena, such as drift and shift, on the agreement between the CGM and a RAPIDLab® 1265 blood gas analyser (BGA). To fulfil this objective, up to 130 patients under intensive care will be fitted with the CGM. Readings from the device taken 8 h after initial placement and calibration will be compared with values measured by a BGA.

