### Secondary outcome measures and endpoints

Secondary outcomes include the following:

• Deteriorations in agreement between the CGM and BGA values measured in the short (1 and 2 h) and medium term (3–8 h) after initial placement and calibration of the CGM

• Agreement beyond point of care, defined as the agreement in blood glucose levels determined by the CGM and a BGA, recorded at 9 and 10 h after the initial placement and calibration of the CGM

• Long term deterioration in agreement measured at 16 and 24 h after initial placement and calibration of the CGM

• Rate of unwanted effects and events defined in DIN EN ISO 14155 2012–01 [Clinical investigation of medical devices for human subjects – Good clinical practice (ISO 14155:2011 + Cor. 1:2011)].

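### The 16 and 24 h deterioration outcome is counted from the first calibration, but the CGM is recalibrated at 8 h, so it does not measure deterioration since that calibration

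*Protocol article*

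**What the plan says.** The Objectives section names the impact of drift and shift on agreement between the CGM and the BGA as part of what the study is to determine.

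Secondary outcome measures and endpoints lists two outcomes after 8 h, both timed from the start of measurement:

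- The later of the two reads: "Long term deterioration in agreement measured at 16 and 24 h after initial placement and calibration of the CGM".
- The earlier one is named as agreement rather than deterioration, and its pairs are those "recorded at 9 and 10 h after the initial placement and calibration of the CGM".

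The same list also covers deterioration at 1 and 2 h and at 3 to 8 h.

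Study period (Visits 2–14), in the text after the Figure 1 caption, says that on the basis of the Visit 10 value "the CGM will be re-calibrated and further values will be recorded at" the four later times. Table 2 likewise marks recalibration at Visit 10. For patients who leave the unit early, the same section provides: "Visit 14 will be brought forward and the CGM will be removed".

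Statistical methods analyses agreement descriptively at each time after placement and calibration, against the 20% bounds of the primary analysis. It limits the linear mixed model to times up to 8 h. Neither the outcome list nor Statistical methods mentions the recalibration.

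**The concern.** The label of the 16 and 24 h outcome and the procedure that produces its readings do not match. The label tells the reader how far agreement has worsened since the device was first calibrated. The procedure adjusts the device at 8 h and then takes the readings, so what is observed is agreement 8 and 16 h after a second calibration.

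Drift and shift are part of the objective, and these are the only scheduled paired readings beyond one 8 h nursing shift. If agreement at 16 or 24 h looked as good as at 8 h, the outcome as named would invite the conclusion that the sensor had held since its first calibration, when the recalibration may have produced the result.

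A smaller, related matter is the moved visit. Eligibility requires only an expected intensive care stay of at least 8 h, and Measurement process lets the length of intensive care set the length of measurement. Some Visit 14 pairs will foreseeably be taken well before 24 h.

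**Working it through.** **Inputs from the protocol.** Recalibration at 8 h (Study period; Table 2). Later paired readings at 9, 10, 16 and 24 h (same places). Margin of 20%, and the planning example of mean δ = 5% and SD σ = 6% for the relative difference (Sample size). The protocol gives no drift rate, so there is no drift figure to reproduce.

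**Check of the planning example.** (δ + 2σ − λ)/√(3σ²/n) with n = 100 is (5 + 12 − 20)/√(3 × 36/100) = −3/1.039 = −2.89. This is below −2.486, as the protocol requires. The present point does not alter this figure; δ and σ are used below only to give a scale.

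**Step 1: time since the last calibration.** For t > 8 h this is t − 8: 9 → 1 h, 10 → 2 h, 16 → 8 h, 24 → 16 h. This step needs no assumption.

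**Step 2: share of drift still visible, assuming linear drift and a full reset at 8 h.** Drift since 0 h is g·t and visible drift is g·(t − 8). The share (t − 8)/t does not depend on the slope g.

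| Reading | Share visible |
|---|---|
| 9 h | 1/9 = 11% |
| 10 h | 2/10 = 20% |
| 16 h | 8/16 = 50% |
| 24 h | 16/24 = 67% |

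**Step 3: illustration against the 20% bound.** Assume also that the 5% mean is reached by drift at 8 h, so g = 5/8 = 0.625% per hour, with SD 6% throughout. The upper limit is mean + 2 × 6%.

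| Reading | Without recalibration | With recalibration |
|---|---|---|
| 16 h | 10.0 + 12 = 22.0% | 5.0 + 12 = 17.0% |
| 24 h | 15.0 + 12 = 27.0% | 10.0 + 12 = 22.0% |

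In this example the 16 h point estimate moves from outside the bound to inside it. At 24 h it is outside either way.

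**Step 4: other assumed drift shapes.**

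- Random walk, SD ratio √((t − 8)/t): 0.33, 0.45, 0.71 and 0.82 at 9, 10, 16 and 24 h.
- Drift that levels off, f(t) = D(1 − e^(−t/τ)), scaled to 5% at 8 h, with τ = 2, 4 or 8 h and visible part f(t) − f(8): at 16 h, 0.1% to 1.8% is visible against 5.1% to 6.8% without recalibration; at 24 h, 0.1% to 2.5% against 5.1% to 7.5%.

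All these shapes give understatement, but all assume that recalibration removes the whole error present at 8 h.

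**The case against.** The other side has good points, and most of them limit the finding.

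- **The 9 and 10 h outcome is called agreement, not deterioration.** This stands. Only its time origin is affected; the deterioration label is at fault for 16 and 24 h alone.
- **The later readings still carry information.** This stands. The 24 h reading comes 16 h after recalibration, the longest interval without calibration among the scheduled pairs. It shows change since recalibration, though not since the first calibration.
- **Drift is already covered before recalibration.** This stands. The 1 to 2 h and 3 to 8 h outcomes, and the mixed model with its 8 h limit, all lie in the first calibration period. The readings after 8 h are only described.
- **The direction of the error is not established.** This stands. No drift rate or shape is given. The text says only that the 8 h value is used, and both BGA and central laboratory samples are drawn then. The Figure 1 caption lists referencing and recalibration as separate steps. The reset may be partial, and a noisy recalibration could add a shift within a patient.
- **The first calibration may serve only as a clock origin, and the recalibration is openly stated.** This stands in part. Describing agreement across a recalibration is a legitimate question of use. But the outcome is named deterioration, and no analysis text separates the two periods.
- **An early Visit 14 falls outside the 24 h ± 30 min window and can be identified.** This stands as far as it goes; the outcome wording does not say what is then done with it.

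A reader might infer that the primary result is contaminated, because Outcome measures and endpoints speaks of at least 8 h. The documents do not support that: the Abstract, Objectives, Primary outcome measure and Statistical methods all put it at 8 h, and Study period has the CGM value recorded at each visit and the 8 h value used for the recalibration.

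**Conclusion.** The point holds as a mismatch between outcome definition and procedure. The 16 and 24 h outcome does not measure deterioration since first calibration; it measures agreement 8 and 16 h after recalibration. Likewise, the 9 and 10 h outcome is agreement 1 and 2 h after recalibration.

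Understatement is conditional. It follows if drift accumulates and recalibration removes at least part of it. With linear drift and a full reset, 50% and 67% of the drift since 0 h would be visible at 16 and 24 h. These are illustrations, because the documents fix neither the drift nor the completeness of the reset.

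Two stronger readings are tempting and not supported. One is that all the later readings say nothing about deterioration or must understate it. The other is that the protocol claims 24 h stability from one calibration; it makes no such claim, though its outcome name invites it.

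The primary 8 h outcome and the 1 to 8 h outcomes are unaffected, provided the 8 h reading precedes recalibration, as the text implies. The power calculation is also unaffected.

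**What to change.** Reconcile the secondary outcome list with Study period and Table 2. Whether and when to recalibrate is for the investigators; the changes below concern outcome definitions and analysis only.

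1. Define the outcomes after 8 h by time since recalibration: 1, 2, 8 and 16 h.
2. Report them separately from the 0 to 8 h data, as a second calibration period.
3. Base any conclusion on drift since the first calibration on 0 to 8 h only.
4. Analyse Visit 14 pairs brought forward for early discharge at their actual time, and leave them out of the 24 h estimate.

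The cost is a change of outcome wording and a little programming, with no new samples. The 24 h estimate will rest on fewer patients. The real price is that nothing can be said about deterioration from a single calibration beyond 8 h.
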